### Outcome measures

Primary outcome is the PBAC score at 24 months of follow-up. Secondary outcomes are patient satisfaction, complications, number of re-interventions, menstrual bleeding pattern, including rates of amenorrhea, QoL, sexual function, sick leave and costs and as predictors of effect of intervention we also measure level of coagulation factors.

### Statistical analysis

#### Sample size

The study is designed as a non-inferiority study. Based on previous studies, we estimate the mean PBAC score at 24 months of follow-up to be 50 points in the LNG-IUS group and 40 points in the endometrial ablation group, with a SD of 40 [23-26].

Previous studies in women with heavy menstrual bleeding have shown that a 50 point difference in PBAC –score between treatments represents a clinically meaningful difference in reduction of menstrual bleeding. In our study we use a non-inferiority marge of 25 points. With this marge and estimated mean PBAC-scores of 50 and 40 points in resp. the LNG-IUS and endometrial ablation group, the estimated scores in both treatment groups will be far below the upper range of normal menstrual blood loss. Using a dropout rate of 15%, an alpha error of 2.5% and Beta error of 20%, we need to include 266 patients (133 patients per treatment group).

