Intrauterine devices were initially introduced as contraceptives, but after the addition of progestagen (LNG-IUS) these devices also reduce menstrual bleeding effectively. The local release of levonorgestrel in the uterine cavity suppresses endometrial growth. A systematic review on the effectiveness of the LNG-IUS in heavy menstrual bleeding concluded that the reduction of menstrual blood loss was 79-96% in the LNG-IUS group [10-13]. In women with heavy menstrual bleeding who presented to primary care providers, the LNG-IUS was more effective than usual medical treatment in reducing the effect of heavy menstrual bleeding on quality of life [14]. However, up to 60% of women discontinue LNG-IUS within 5 years because of unscheduled bleeding, pain, and/or systemic progestogenic side-effects [15]. In the Royal College of Obstetricians and Gynaecologists (RCOG) guideline on heavy menstrual bleeding, the use of the LNG-IUS is the first therapeutic option when drug treatment has failed. This is not based on proven cost-effectiveness [15].

Endometrial destruction techniques, which aim to destroy or remove the endometrial tissue, have become alternatives to hysterectomies. In 1991 in the Netherlands 21,433 hysterectomies were performed, a number that was reduced to 16,320 in 1998 and just above 11,000 in 2010, which was partly due to the start of using endometrial ablation [16]. Approximately 47-58% percent of women report an amenorrhea after treatment with the bipolar ablation device [5,17-20]. The satisfaction rates of endometrial ablation have been evaluated by several randomised controlled trials and is showing a rate of about 90% [19,21,22]. Ablation techniques result in shorter duration of surgery, shorter hospital stay and quicker recovery time compared to hysterectomy.

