Seven trials compared the LNG- IUS with transcervical resection of the endometrium or balloon abaltion. In the meta-analyses a significant lower mean pictorial blood chart score (PBAC) was reported for all women and a significant lower mean reduction in pictorial blood chart score was reported in the surgical group. One study showed a significantly lower median PBAC score in the LNG-IUS group at nine months and one year follow-up 23. Further outcomes showed no difference in satisfaction rates, amenorrhea rates, duration of menstruation, further surgical treatment or quality of life (QoL). Nevertheless, the studies are small, most studies have a short period of follow-up and contain a lot of non-compliance, which makes interpretation of outcomes difficult [12,20,23-27].

Consequently, usual care in the Netherlands implies one of these two strategies for the treatment of heavy menstrual bleeding if drug therapy fails. The strategy LNG-IUS means prescription and placement by the general practitioner (GP) or gynaecologist without anaesthesia. The strategy endometrial ablation implies performing an endometrial ablation by a gynaecologist in day-care or outpatient clinic with or without general anaesthesia. Due to lack of sufficiently powered studies directly comparing LNG-IUS with endometrial ablation, there is currently no evidence based advice for the use of one of these treatment possibilities.

We propose a randomised controlled trial in which these two strategies are compared in the treatment of heavy menstrual bleeding. The study will focus on (cost-) effectiveness, patient satisfaction and QoL.

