### Interventions

The LNG-IUS can be placed either by a GP or by a gynaecologist. In the endometrial ablation group, a second generation bipolar ablation technique (Novasure) will be performed by a gynaecologist.

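### The planning SD of 40 fits poorly with the protocol's own 47-58% amenorrhoea after bipolar ablation, so the stated 80% power is probably optimistic and is not met above 50%

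*Protocol article*

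**What the plan says.** Under Sample size, the protocol article states that "The study is designed as a non-inferiority study". For the 24-month PBAC it assumes "40 points in the endometrial ablation group, with a SD of 40"; the matching LNG-IUS mean is 50. A single SD is given, which I read as common to both arms. The margin is 25 points and the dropout allowance 15%. The result is stated as "an alpha error of 2.5% and Beta error of 20%, we need to include 266 patients", or 133 per arm. Under Outcome measures, "Primary outcome is the PBAC score at 24 months of follow-up".

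Two other sections bear on the SD. The Background reports that "Approximately 47-58% percent of women report an amenorrhea after treatment with the bipolar ablation device", with no time point. The Interventions section confirms that in this trial "a second generation bipolar ablation technique (Novasure) will be performed by a gynaecologist".

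The planning means and SD are referenced to studies 23-26. All four belong to the set that the Background introduces with "Seven trials compared the LNG- IUS with transcervical resection of the endometrium or balloon abaltion", so the planning figures appear to come from ablation techniques other than the one used here.

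**The concern.** A woman with no menses scores zero on a pictorial blood-loss chart. If about half of the ablation arm scores zero and the arm mean is still 40, the women who bleed must average about 80. That two-part mixture has a large SD before any variation among the bleeders is counted. The protocol nowhere reconciles its SD of 40 with its own amenorrhoea rate.

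In a non-inferiority trial, a planning SD that is too small means a wider confidence interval than intended and a greater chance that it crosses the margin although LNG-IUS is acceptable. A reader who trusts the stated 80% could then take an inconclusive result as a well-powered negative one.

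**Working it through.** **1. Inputs.** Means 50 and 40, SD 40, margin 25, alpha 2.5%, beta 20%, dropout 15%, total 266 (Sample size). Allocation 1:1 (Patient recruitment, randomization and collection of data). Amenorrhoea share p from 0.47 to 0.58 (Background).

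**2. Reproducing 266.** The planned true difference is 50 - 40 = 10, so the distance to the margin is 25 - 10 = 15. Alpha is taken as one-sided, because that reproduces the figure.
- Normal approximation: n = 2·40²·(1.960 + 0.842)²/15² = 111.6, so 112 per arm. Then 112/0.85 gives 132 per arm, 264 in total.
- Noncentral t: 113 per arm (power 80.1%). Then 113/0.85 = 132.9, so 133 per arm, 266 in total.

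The stated figure is exact on its own inputs.

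**3. Smallest possible SD.** Let a share p score 0, let the arm mean be 40, and let CV be the coefficient of variation among women who still bleed. Their mean is 40/(1-p), and

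SD² = 40²·[(1 + CV²)/(1-p) - 1].

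The minimum is at CV = 0, where every bleeding woman has the same score: SD_min = 40·√(p/(1-p)).

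- p = 47%: 40·√(0.47/0.53) = 37.7
- p = 50%: 40·√1 = 40.0
- p = 52.5%: 40·√(0.525/0.475) = 42.1
- p = 58%: 40·√(0.58/0.42) = 47.0

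**4. What SD 40 requires.** Setting SD = 40 gives CV² = 2(1-p) - 1. At 47% this is 0.06, so CV is about 0.24: an SD of about 18 among bleeders who average 75. At 50% it is 0. Above 50% it is negative, so no distribution satisfies it.

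**5. Power.** The ablation SD is s, the LNG-IUS SD is kept at 40, and there are 113 evaluable women per arm. The standard error is √((s² + 40²)/113), the noncentrality is 15/SE, with 224 degrees of freedom and one-sided 2.5%. Example at 58% and CV 0: SE = √((47.0² + 40²)/113) = 5.81, 15/5.81 = 2.58, power 73%.

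| Amenorrhoea | Mean of bleeders | SD, CV 0 (bound) | Power | SD, CV 0.3 | Power | SD, CV 0.5 | Power |
|---|---|---|---|---|---|---|---|
| 47% | 75.5 | 37.7 | 82% | 41.1 | 79% | 46.6 | 73% |
| 50% | 80.0 | 40.0 | 80% | 43.5 | 77% | 49.0 | 71% |
| 52.5% | 84.2 | 42.1 | 78% | 45.5 | 75% | 51.1 | 69% |
| 58% | 95.2 | 47.0 | 73% | 50.5 | 69% | 56.2 | 63% |

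The CV 0 columns need only the assumptions about p, the zero score and the mean. The values 0.3 and 0.5 are my assumptions; the protocol gives no spread among bleeders.

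**The case against.** Much can be said for the protocol, and several stronger readings fail.

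- A reader might infer that 266 is miscalculated. It is not: the inputs conflict with the Background, while the arithmetic is right.
- A reader might infer that SD 40 is at or below the minimum over the whole 47-58% range. At 47-49% the minimum is 37.7 to 39.2, so SD 40 is feasible there. At 47% the bound alone gives 82% power, and any shortfall at 47-50% depends on spread among bleeders that the document does not report.
- A reader might carry the larger SD into both arms, which gives 67% power at 58% on the bound and about 52% with CV 0.5. No LNG-IUS amenorrhoea rate is given, so the documents do not support this. The Background reports only that earlier trials found no difference in amenorrhoea, and those used other ablation techniques.
- A reader might argue that lowering the ablation mean cannot rescue SD 40. At 58% that needs a mean of about 34. With LNG-IUS fixed at 50 the difference becomes 16, and power falls to 39%. But this holds only if the LNG-IUS mean stays at 50. Were both means lower, the 10-point difference could survive.
- The 47-58% is approximate and undated, and women may switch treatment before 24 months. The share at zero at the primary time point is therefore unknown.
- The Data analysis section names the Mann-Whitney test for non-normal variables, whereas these powers are for a t-test on means. That is, however, the framework that reproduces 266 and in which the margin is expressed.
- The final confidence interval will reflect the observed SD whatever was planned. That protects the estimate but does not make the power statement correct.

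These points limit the claim. They do not remove the conflict over most of the quoted range.

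**Conclusion.** The concern holds in a limited form. The sample size is correct on its inputs, but the combination of mean 40, SD 40 and 47-58% amenorrhoea is impossible above 50% and strained from 47% to 50%. On the bound alone, power runs from 82% down to 73%. It is below 80% at every rate above 50%, and modest assumed spread (CV 0.3) puts it below 80% across the whole range. The stated 80% is best described as probably optimistic, not as disproved throughout.

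This rests on four assumptions: amenorrhoea scores PBAC 0, the 47-58% applies at 24 months, the ablation mean is 40 with LNG-IUS at 50, and the LNG-IUS SD is 40.

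**What to change.** Keep the 266 women and make four changes.

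1. Reconcile the planning mean and SD for the ablation arm with the amenorrhoea rate quoted for the bipolar device, and say which rate is expected at 24 months.
2. Replace the single 80% with power over a range of SDs, flagging SD 40 as optimistic. With 113 evaluable per arm, a 10-point difference and the LNG-IUS SD at 40, ablation SDs of 40, 47, 50 and 56 give 80%, 73%, 70% and 64%.
3. Compute the SD of 24-month PBAC over both arms together, blinded to allocation, and report it beside the planning value. A 10-point difference between arms adds only 5² = 25 to the variance (√1625 = 40.3 instead of 40), so the comparison is fair.
4. Specify a primary model for the difference in mean PBAC, adjusted for baseline PBAC. The Data analysis section names no such model, and baseline PBAC is already collected before randomisation. The variance falls by a factor of about 1 - r², where r is the correlation between baseline and 24-month scores. The document gives no r, so the gain cannot be promised.

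The cost is a less favourable power statement, one blinded calculation and one sentence on the primary model. No extra women and no new measurements are needed.

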#### Data analysis

Data will be analysed according to the intention to treat principle. Statistical analysis will be performed using the software Statistical Package for the Social Sciences (SPSS, Inc., Chicago, IL, USA).

Point estimates and 95% confidence intervals will be calculated for different time points.

First, the treatment effect at 24 months of follow-up of a strategy starting with LNG-IUS compared to a strategy starting with endometrial ablation will be investigated. For not normally distributed continuous variables, differences between groups will be tested with the Mann–Whitney U test. Differences between categorical variables will be tested with the Chi-square test or Fisher’s exact test. Secondary, to assess the treatment effect over time, and the interaction of the intervention effect, we will use a mixed effects model. Time to re-intervention will be compared with Kaplan Meier analysis and Cox regression.

The analysis of the influence of lower levels of coagulation on the treatment effect of LNG-IUS and endometrial ablation will be explorative.

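### The trial is sized for non-inferiority on mean PBAC (25-point margin), but the Data analysis section does not use the margin, and its only named test for skewed outcomes is Mann-Whitney U

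*Protocol article*

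**What the plan says.** The Outcome measures section names one primary endpoint: "Primary outcome is the PBAC score at 24 months of follow-up".

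The Sample size section states the design, "The study is designed as a non-inferiority study", and the margin, "In our study we use a non-inferiority marge of 25 points". It expects the scores "to be 50 points in the LNG-IUS group and 40 points in the endometrial ablation group, with a SD of 40". With 2.5% alpha, 20% beta and 15% dropout, it arrives at 266 women, 133 per arm.

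The Data analysis section specifies intention to treat and then says "Point estimates and 95% confidence intervals will be calculated for different time points". It takes the 24-month comparison of the two strategies first. The next sentence gives the rule for skewed data: "For not normally distributed continuous variables, differences between groups will be tested with the Mann–Whitney U test". Chi-square or Fisher's exact tests follow for categorical variables. A mixed effects model is a secondary step for the effect over time. Neither non-inferiority nor the 25-point margin appears in this section.

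**The concern.** The design asks whether mean PBAC after starting with LNG-IUS is at most 25 points worse than after starting with ablation. The test that the analysis section would apply to a skewed score asks whether the two distributions are the same.

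- A non-significant Mann-Whitney result does not show non-inferiority.
- A significant one does not show that the margin was exceeded.
- The alpha and power behind the 266 women belong to a comparison of means against a margin, so they do not carry over to this test.

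If the text does not say which result decides, the conclusion could rest on either one, and the choice could be made after the data are seen.

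**Working it through.** **1. Reproduce the sample size.** Inputs from the Sample size section: margin 25, expected difference 50 − 40 = 10, SD 40, alpha 2.5% (taken as one-sided), power 80%, dropout 15%.

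- Normal approximation: n per arm = 2 × (1.96 + 0.8416)² × 40² / (25 − 10)² = 111.6, so 112.
- With the t distribution: 112 per arm gives 79.8% power and 113 gives 80.1%, so 113.
- Dropout: 113 / 0.85 = 132.9, so 133 per arm and 266 in total. This matches the stated figure exactly.

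Other readings do not match. A two-sided 2.5% alpha gives 160 per arm after dropout, and an expected difference of 0 gives 49. A superiority test of the expected 10 points on means would need 252 evaluable per arm (252 / 0.85, so 297 per arm, 594 in total). At 113 per arm that test has about 47% power. The trial is therefore powered for a mean difference read against 25.

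**2. Would PBAC fall under the Mann-Whitney rule?** PBAC cannot be below 0. A normal distribution with SD 40 would put 16% of women below 0 at mean 40 (z = −1.00) and 11% at mean 50 (z = −1.25). The Background also reports amenorrhoea in 47–58% after bipolar ablation, the technique used here. A skewed score is very probable.

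**3. What the promised interval could do.** With 113 per arm, SE = 40 × √(2/113) = 5.32. The two-sided 95% half-width is 1.96 × 5.32 = 10.4 points. Comparing its upper limit with 25 is the one-sided 2.5% test that the sample size assumes.

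**4. How far the two procedures diverge.** Simulated trials with 113 per arm and means 50 and 40. The distribution shapes are assumptions, since the protocol gives only means and SD. The confidence-interval rule declares non-inferiority in about 80% throughout.

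| Assumed shape | Mann-Whitney significant against LNG-IUS | Significant and non-inferior by CI |
|---|---|---|
| Gamma, SD 40 in both arms | 75% | 56% |
| Zero-inflated gamma, 20–30% zeros, SD 40 | 55–57% | 36–38% |
| Gamma, equal CV (SDs about 44 and 36) | 39% | 21–22% |

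A lognormal shape gives more (85% and 66%), but it allows no zeros and so fits this outcome poorly.

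With equal means (40 and 40, gamma, SD 40), the interval rule declares non-inferiority in about 99% of trials and Mann-Whitney is significant in about 5%.

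**The case against.** Three objections carry weight.

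**The intervals are there.** The section promises point estimates and 95% intervals, and a 95% interval on the mean difference matches the 2.5% alpha. A reader might infer that the plan contains only superiority tests and cannot answer the non-inferiority question. The text does not support that: the interval could answer it. What stands is that the intervals are not said to be for the between-arm mean difference and are not tied to the margin.

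**The Mann-Whitney sentence is generic.** It does not name PBAC, and it also serves quality of life, sexual function, sick leave and costs. Routing the primary endpoint to it is an inference. But it is a strong one: the sentence directly follows the one on the 24-month comparison, and no other test is named for a continuous outcome at a single time point. The mixed model could give a 24-month estimate but is placed second, for the effect over time.

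**This is an article.** An explicit decision rule may stand in a full protocol or analysis plan that is not shown, and its absence alone would not be a finding. Naming a test that does not fit the design set out one subsection earlier is a different matter, because that is in this text.

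Two stronger claims about size also fail:

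- **That the likeliest result is a contradiction.** The joint frequency depends on shape and is below half in two of the three rows above. A result that is statistically worse but within the margin is also a recognised non-inferiority outcome. The interval alone (above 0 and below 25) gives it in about 28% of trials at the design values.
- **That Mann-Whitney would usually miss a true difference at the margin.** This needs a case such as 50% zeros in each arm with means 65 and 40 and a CV of 0.75 among women who bleed. That case implies SDs of about 95 and 58, not 40. At SD 40 with a gamma shape, Mann-Whitney is significant in about 100% of trials at that difference.

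**Conclusion.** The point holds in this form: the named test does not match the design, and the promised intervals are not linked to the margin. The sample size itself is sound and reproduces exactly.

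At the planned means, the interval rule declares non-inferiority in about 80% of trials. Mann-Whitney is significant against LNG-IUS in about 40–75%, and both happen together in about 22–56%. These ranges rest on assumed gamma-type shapes with SDs at or near the planned 40 and on 113 evaluable women per arm. That PBAC falls under the Mann-Whitney rule is very probable on the protocol's own figures but is not stated. The documents do not show that the trial is unable to answer its question, only that this section does not say which result will answer it.

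**What to change.** In the Data analysis section, state that the primary analysis estimates the difference in mean PBAC at 24 months (LNG-IUS minus ablation) with a two-sided 95% confidence interval, using robust or bootstrap standard errors because of the skew. State that LNG-IUS is declared non-inferior only if the upper limit is below 25 points. Keep Mann-Whitney U for PBAC as a supportive analysis without a role in the non-inferiority decision. If a fuller plan already contains this rule, bring the text into line with it.

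The cost is a few sentences. No further data are needed, the sample size stays at 266, and the primary analysis then has the alpha and power on which that number was based.

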### Economic evaluation

The economic analysis will be conducted from a societal perspective including direct medical and direct and indirect non-medical costs. Relevant direct costs components that will be taken into account are costs of the LNG-IUS and endometrial ablation, interventions for complications, hospital admission and home care, consisting of both professional care as well as informal care. Sick leave and loss of productivity at work will be taken into account as indirect non-medical costs.

The economic evaluation will be designed as a cost-effectiveness analysis, with the costs per treatment resulting in a reduction of menstrual blood loss as an outcome measure. We will also perform a cost-utility analysis expressing the incremental costs per Quality Adjusted Life Years based on the SF-36. Robustness of the results (costs and health outcomes) for various assumptions and parameter estimates will be explored in sensitivity analyses and visualized in ICER-graphs and cost-effectiveness acceptability curves.

## Discussion

In view of its high prevalence, an optimal treatment for heavy menstrual bleeding is of utmost importance. Usual care in The Netherlands implies two strategies for the treatment of heavy menstrual bleeding if drug therapy fails: first, there is the LNG-IUS that can be applied easily by the GP, which saves costs, but has considerable failure rates. As an alternative, endometrial ablation is also very effective, but this treatment has to be performed by a gynaecologist. Large randomised controlled trials comparing LNG-IUS with endometrial ablation are lacking and hence no preferred advice for the use of one of these treatment possibilities is available. When we estimate that treatment for heavy menstrual bleeding involves 10,000 women annually, there can be a potential saving from implementing the best strategy as appears from the proposed study. Therefore, a direct comparison of both strategies on cost-effectiveness is essential to determine which strategy should be advocated.

This is the first study comparing LNG-IUS and endometrial ablation which will be organized in a network infrastructure in which both GP’s and gynaecologists collaborate. It has got the largest study population compared to other trials and has a longterm follow-up of 2 years. Besides the objective outcome PBAC we also measure patient satisfaction, QoL and sexual function. Due to this study design and outcome measures, the results will be applicable for a large group of women suffering from heavy menstrual bleeding.
